#### Bidirectional Exposure Analysis to Assess Signal Robustness

We will specifically highlight instances where the addition of drug B to drug A, and, conversely, drug A to drug B, yield concordant results for the outcome of interest. Observing consistent effects in both directions, particularly for chronic medications, will strengthen confidence in the validity of the signal and suggest that findings are less likely to be explained by residual confounding or treatment selection bias.

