#### Cohort Entry Dates for Exposed and Referent Groups

The exposed group will comprise regular users of drug A and new users of drug B, as described earlier. The cohort entry date for individuals in the exposed group will be the start date of drug B. The referent group will comprise regular users of drug A who are not coprescribed drug B. The cohort entry date for individuals in the referent group will be assigned based on the distribution of the time differences between the most recent prescription for drug A and the initiation of drug B for individuals in the exposed group, ensuring similar observation periods between groups [25].

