#### Individual-Level Exclusion Criteria Applied to the Exposed and Referent Groups

We will exclude individuals who meet any of the following criteria:

Individuals prescribed drug B within 180 days before the cohort entry date (to ensure those in the exposed group are new users of drug B and that those in the referent group were not previously exposed).Individuals prescribed another medication in the same class as drugs A and B on the cohort entry date. For example, if drug A or B is sertraline, which is a serotonin reuptake inhibitor (SSRI), individuals prescribed a nonsertraline SSRI on the cohort entry date will be excluded.Individuals discharged from the hospital or emergency department within 2 days before the cohort entry date (to ensure that prescriptions are new outpatient prescriptions).Individuals whose day supplies for drug A or B are ≥100 days or <2 days.Individuals who are nonpermanent Ontario residents, are aged <66 or >105 years on the cohort entry date, or have a date of death on or before the cohort entry date (data cleaning exclusions).

An individual can only enter a cohort once; if an individual meets the eligibility criteria multiple times, the first eligibility date will serve as the cohort entry date.

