#### Criteria for Identifying Potential Signals of Harmful DDIs

Associations between a drug pair and an adverse outcome that meet the following criteria will be considered potential signals of harm and analyzed further:

Thresholds for RRs and RDs. The lower bound of the 95% CI for the RR must be ≥1.33, and for the RD, it must be ≥0.1%. These thresholds were chosen to ensure that only clinically significant increases in risk (of sufficient magnitude to be of concern) are considered. This analysis will focus solely on potential harms from drug combinations rather than protective benefits.Statistical significance. The *P* values from the modified Poisson regression model (for RRs) and the binomial regression model (for RDs) must be statistically significant after applying the Benjamini-Hochberg correction. This correction accounts for multiple comparisons across all outcomes and drug pair cohorts. The false discovery rate will be set at 5%, and the highest *P* value below the Benjamini-Hochberg critical value will be considered statistically significant, along with all *P* values below it. This correction will minimize the risk of false-positive discoveries (type I errors).

Drug pair cohorts that do not generate significant signals will not undergo further analysis.

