Survival analysis. To assess whether the initial signal persists when analyzed using a time-to-event approach, we will conduct a Cox proportional hazards regression with a 30-day follow-up period, censoring on death when all-cause mortality is not the outcome of interest. We will test the proportional hazards assumption by including an interaction term between the new-user status and follow-up time. This analysis will help determine whether the signal is robust across different modeling techniques.Negative-control exposure analyses. To detect potential biases from unobserved confounders, we will perform negative-control exposure analyses. A negative-control exposure is a variable that shares the same sources of bias as the drug of interest but cannot plausibly cause the outcome. We will rerun the regression analyses for the initial signals using a control exposure period starting 90 days before cohort entry [37]. This analysis will help identify any confounding factors that may have influenced the initial signal. Notably, the outcome of all-cause mortality cannot be examined with this method, as all patients lived to their cohort entry date. A positive association (ie, RRs and RDs significantly different from null, with *P*<.05) in this analysis would suggest potential confounding, whereas the absence of an association would bolster the credibility of the original signal.E-value analysis. We will conduct E-value analyses to quantify the minimum strength of association an unmeasured confounder would need to have with both the drug combination and the outcome to negate the observed signal [38]. Larger E-values indicate that substantial unmeasured confounding would be required to explain away the signal, whereas smaller E-values suggest that minimal unmeasured confounding could do so. For an initial signal to be considered robust, the E-value must exceed 2.Propensity score matching. To further validate the robustness of the signal, we will use 1:1 propensity score matching to balance the exposed and referent groups on baseline characteristics [39]. This method estimates the average treatment effect in the treated and mitigates the influence of extreme weights, which can occur with IPTW. Consistency between the results of this analysis and the initial findings will strengthen the validity of the signal.Bootstrap analysis. We will use a multiplier bootstrap procedure to compute RRs and RDs across 200 random samples, each of the same size as the original cohort. This method helps correct SEs and CIs, ensuring they have the correct coverage rates [36,40]. For the signal to be considered robust, at least 90% of the bootstrap samples must yield results consistent with the original findings, with *P*<.05 and CIs for RRs and RDs in the same direction as initially observed.

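### Agreement between the two initiation orders argues only against confounding that differs between the orders, not against confounding by an indication that both drugs share

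*Protocol article*

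**What the plan says.** The section Bidirectional Exposure Analysis to Assess Signal Robustness will highlight pairs whose two initiation orders agree on an outcome. It states: "Observing consistent effects in both directions, particularly for chronic medications, will strengthen confidence in the validity of the signal", and adds that such agreement will "suggest that findings are less likely to be explained by residual confounding or treatment selection bias". It does not limit this to pairs with different indications and does not define concordant.

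The contrast behind each order is set out under Cohort Entry Dates for Exposed and Referent Groups. "The cohort entry date for individuals in the exposed group will be the start date of drug B", and "The referent group will comprise regular users of drug A who are not coprescribed drug B". Each order therefore compares people who add a second drug with people who do not; there is no active comparator.

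The class exclusion removes this group: "Individuals prescribed another medication in the same class as drugs A and B on the cohort entry date". It concerns a further drug in the class of A or B. It does not address A and B treating the same condition.

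**The concern.** Suppose A and B both treat the same progressive condition. When the disease worsens, users of A are given B and users of B are given A. Both cohorts then compare worsening patients with stable ones, and both risk ratios rise even if neither drug nor the pair has any effect. Agreement is then what confounding alone predicts, so it cannot count against that confounding.

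The emphasis on chronic medications does not help. Chronic use is not the property that makes agreement informative; a difference in indication is. Stepwise add-on treatment of one chronic disease is a natural source of shared confounding. At stake is how much readers may conclude from the highlighted pairs.

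**Working it through.** The protocol gives no figure for this analysis, so there is none to reproduce. The inputs on worsening below are assumptions. They show the mechanism and do not estimate its size in the Ontario data.

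**1. One order, unadjusted, no drug effect.** Assume that 10% of users are worsening, that the second drug is started in 30% of worsening and 3% of stable users, and that the 30-day risk is 10% against 2%.
- Starters: 0.10 × 0.30 + 0.90 × 0.03 = 0.057.
- Worsening among starters: 0.030 / 0.057 = 52.6%. Among non-starters: 0.070 / 0.943 = 7.4%.
- Risks: 0.02 + 0.08 × 0.526 = 6.21%, and 0.02 + 0.08 × 0.074 = 2.59%.
- RR = 6.21 / 2.59 = 2.39. With the same inputs in the other order, it is 2.39 there too.

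**2. How often the second order also meets the signal thresholds.** The criterion is: "The lower bound of the 95% CI for the RR must be ≥1.33, and for the RD, it must be ≥0.1"%. Take 583 exposed, the median number of new users in the Results section, and assume 4 referents each (2332).
- SE(log RR) = √[(1 − 0.0621)/(583 × 0.0621) + (1 − 0.0259)/(2332 × 0.0259)] = 0.205.
- (ln 2.39 − ln 1.33)/0.205 − 1.96 = 0.91, so the RR limb is met about 82% of the time. Simulating both limbs together gives about 80%. The Benjamini-Hochberg step is not applied.

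If the two cohorts are independent, this is also the probability for the second order given a signal in the first.

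**3. Smaller residual imbalance after weighting.** Keep the risks and the 4:1 ratio.
- Worsening in 30% against 10%: risks 4.4% and 2.8%, RR 1.57. At 583 exposed the SE is 0.228, and (ln 1.57 − ln 1.33)/0.228 − 1.96 = −1.23, or about 11% (12% by simulation). At 2130 exposed it is about 29%. The point estimate still lies above 1 with z = 0.452/0.228 = 1.98, or about 98% by this approximation.
- Worsening in 20% against 10%: risks 3.6% and 2.8%, RR 1.29. The thresholds are met about 2% of the time at 583 and 1% at 2130.

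**4. Shared, unequal and one-drug confounding.** A separate simulation used 400 repetitions, 40,000 users per order, 2% baseline risk, 10% worsening, a fourfold outcome risk when worsening, and no drug effect.

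| Who starts the add-on (worsening vs stable) | Mean RR, two orders | Both orders meet thresholds |
|---|---|---|
| 20% vs 3% in both orders | 1.83 and 1.82 | 63% |
| 20% vs 3%, and 12% vs 3% | 1.81 and 1.52 | 13% |
| 20% vs 3%, and no dependence on worsening | 1.81 and 1.02 | 0% |

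The last row shows what the check can detect, and the first row what it cannot.

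**5. Whether the other safeguards cover the gap.**
- Negative-control exposure: "We will rerun the regression analyses for the initial signals using a control exposure period starting 90 days before cohort entry". This can pick up a stable difference in disease severity, but can miss worsening that arises near the add-on date. The protocol notes that it cannot examine mortality.
- E-value: "For an initial signal to be considered robust, the E-value must exceed 2". For RR 1.33 the E-value is 1.33 + √(1.33 × 0.33) = 1.99, so this adds almost nothing to the threshold already applied.
- Challenges and Limitations acknowledges residual confounding in general terms only.

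**The case against.** The strongest reply has four parts.

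First, the sentence is hedged: it says less likely, not excluded. Across unselected pairs it is fair, because confounding tied to one drug is screened out (0% in the last row above). This stands, and it is why the analysis should be kept.

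Second, the 80% figure is a high case. It assumes no adjustment, although the propensity score uses more than 400 characteristics, and equal confounding in both orders. This also stands: steps 3 and 4 show much lower frequencies once either assumption is relaxed. What remains is agreement in direction, and because concordant is not defined, agreement in direction might qualify.

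Third, chronic medications are not the same as add-on pairs for one disease. The protocol's own chronic-chronic example, levothyroxine with rosuvastatin, is not an obvious shared-indication pair. So the text does not place its emphasis exactly where the check is weakest. It places it on a property that does not separate the informative pairs from the uninformative ones.

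Fourth, a reader might infer that concordant signals form a most-trusted list, so that confounded pairs are upgraded rather than filtered out. The documents do not support that. Concordance is not among the criteria for potential signals, is not named in Step 1 of the validation framework, and is not a criterion in Table 2. Highlighted signals still go through the sensitivity analyses and the pharmacological and epidemiological review.

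**Conclusion.** The point holds in a limited form. As written, the inference extends to pairs for which it has no basis: those whose drugs treat the same or related conditions. For the rest it is reasonable. The consequence is over-crediting of some highlighted signals; no estimate, threshold or selection step is altered.

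The size depends on assumptions that the documents cannot settle. With strong, unadjusted and equal confounding, the second order meets the thresholds about 80% of the time at 583 exposed. With a residual imbalance of 30% against 10% it does so about 12% of the time, and with 20% against 10% about 2%. A reader might go further and conclude that concordance carries no information against confounding at all. That follows only if the confounder is assumed to produce the same RR in both orders as a true effect would; it is then true by construction and does not measure the value of the check in general.

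**What to change.** In the bidirectional section:

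1. Limit the inference to residual confounding or selection that differs between the two initiation orders.
2. Among the concordant signals only, flag pairs whose drugs share an indication. Report both directions descriptively for these pairs, and state that agreement does not count against residual confounding there. Base the flag on indication, not on the drug-class list used for the exclusion criterion, because drugs of different classes can treat the same condition.
3. Replace the emphasis on chronic medications with an emphasis on drugs with different indications.

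The cost is a change of wording and indication coding for the concordant signals, not for all of the roughly 200,000 pairs. Fewer signals will be credited by concordance. No cohort, model or estimate changes.

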#### Exploring the Data Using Interactive Visualization

To facilitate data exploration, we will develop an interactive visualization tool. The tool will enable users to visually explore the outputs from our analyses, providing an overview of the data with the ability to access, filter, and modify the displayed information [43,44]. Users will be able to apply filters based on RRs or other metrics to identify associations that meet specific criteria. The tool will support manual exploration, enabling users to interactively query and sort the data.

#### Overall Framework to Identify, Characterize, and Validate Signals of Harmful DDIs

Signals identified in the high-throughput computing analysis will be rigorously evaluated for clinical relevance by examining evidence from PK, PD, and epidemiological studies, as well as by using clinical validation tools to prioritize and confirm the most clinically significant interactions as follows (Figure 2):

Step 1: signal identification. Signals of potentially harmful DDIs identified in the high-throughput analysis must (1) meet predefined thresholds for RRs and RDs, (2) remain statistically significant after the Benjamini-Hochberg correction for multiple comparisons, and (3) be supported in sensitivity and bias analyses.Step 2: PK and PD assessment. PK and PD evidence will be evaluated to assess the biological plausibility of the interaction. For PK assessment, published studies on enzyme inhibition, drug metabolism, and clearance will be reviewed. For example, sulfamethoxazole inhibits CYP2C9, which metabolizes warfarin, leading to increased warfarin levels and a higher risk of bleeding [11,45]. For PD assessment, synergistic and antagonistic interactions will be examined. For example, the concurrent use of two antiplatelet agents can increase the risk of bleeding.Step 3: cross-validation with drug interaction checkers and product monographs. Signals will be cross-validated using DDI checkers, such as Lexicomp, Micromedex, and Drug Interaction Facts, along with regulatory product monographs (eg, from Health Canada and the US Food and Drug Administration [FDA]). Interaction severity will be classified as major, moderate, or minor based on standardized clinical guidelines. Recommended interventions for major interactions include (1) avoiding coadministration, (2) adjusting doses, and (3) monitoring relevant biomarkers (eg, the International Normalized Ratio [INR] for warfarin interactions).Step 4: prioritization of high-quality epidemiological evidence. Evidence from epidemiological studies will be examined and prioritized as randomized controlled trials (RCTs), high-quality cohort studies, and case-control studies. We will also prioritize evidence from studies of vulnerable populations (eg, older adults, patients with chronic kidney disease, and polypharmacy cohorts).Step 5: alternative evidence when high-quality epidemiological studies are unavailable. Complementary signal detection methods (eg, disproportionality analyses of pharmacovigilance databases, such as FAERS and VigiBase), case reports, and case series will be reviewed to assess the interaction’s potential clinical significance when high-quality epidemiological evidence is unavailable. For disproportionality analyses, pharmacovigilance databases (eg, FAERS, VigiBase) will be analyzed to determine whether drug coadministration is disproportionately associated with adverse events compared to the administration of a single medication. When large-scale epidemiological data are lacking, case reports and case series may provide supporting evidence.Step 6: final signal validation and decision-making. Evidence from PK, PD, and epidemiological studies, pharmacovigilance data, and clinical decision-support tools will be synthesized to assess the credibility of the signal.

**Figure 2 figure2:**
[figure not shown]
Framework to identify, characterize, and validate signals of harmful DDIs. DDI: drug-drug interaction; PD: pharmacodynamic; PK: pharmacokinetic; RD: risk difference; RR: risk ratio.

Each signal will be independently reviewed by two reviewers using the aforementioned criteria. The reviewers will classify each signal based on the strength and consistency of supporting data as an evidence-supported signal, an emerging evidence signal, or a signal with no supporting evidence. To minimize subjectivity, we will calculate an interrater agreement measure (eg, Cohen κ) to assess the level of concordance between the reviewers and determine whether they reach the same conclusion [46,47]. Any discrepancies will be resolved through discussion and, if needed, adjudicated by a third reviewer.

The criteria for classifying a signal as an evidence-supported signal (regulatory and clinical action may be warranted), an emerging evidence signal (additional investigation will be performed), or a signal having no supporting evidence (no further studies will be performed) are summarized in Table 2. Briefly, a signal will be considered evidence supported if multiple lines of evidence support a causal effect, it will require further study if the existing evidence is conflicting, and it will be dismissed in the absence of supportive evidence.

**Table 2 table2:** Summary table for criteria for signal confirmation, further study, or dismissal.

Category and criteria		Key indicators	Next steps
**Evidence-supported signal^a^ (low priority for further investigation)**			
	Multiple independent sources align	PK^b^/PD^c^ evidence supports a plausible interaction. High-quality epidemiological data (RCTs^d^, cohort studies) confirm increased risk. Product monographs or clinical decision-support tools (eg, Lexicomp) classify it as a major interaction.	Regulatory and clinical action may be warranted, such as labeling changes or guideline updates.
**Emerging evidence signal^a^ (additional investigation to be performed)**			
	Conflicting evidence	PK/PD data suggest a risk, but epidemiological studies do not confirm it. Epidemiological findings are inconsistent or based on low-quality studies (eg, small sample size, case reports only). Product monographs or clinical decision support tools give mixed or uncertain classifications.	A pharmacoepidemiological study should be conducted.
	Limited population-specific data	High-risk populations (patients with chronic kidney disease, older adults, polypharmacy patients) are underrepresented in studies. Current evidence is based on general population data but lacks subgroup analyses.	A pharmacoepidemiological study should be conducted.
	Emerging signal in pharmacovigilance databases	Disproportionality analysis (eg, FAERS, VigiBase) suggests a safety concern but lacks validation in clinical studies. Case reports describe severe but rare adverse events needing further confirmation.	A pharmacoepidemiological study should be conducted.
**No supporting evidence for signal^a^ (no further studies to be performed)**			
	No clear biological or clinical risk	There is a lack of PK/PD plausibility (eg, drugs do not share metabolic pathways or receptor targets). There is no statistically significant association in large epidemiological studies. There are no case reports/case series. Product monographs or clinical decision-support tools classify it as a low-risk (minor) interaction or report no interaction.	No further action is needed.

^a^Signals retained after Benjamini-Hochberg correction for multiple comparisons.

^b^PK: pharmacokinetic.

^c^PD: pharmacodynamic.

^d^RCT: randomized controlled trial.

#### Exploring Harmful DDIs Using Machine Learning

We will explore an alternative strategy for further investigating harmful DDIs using a machine learning algorithm. This complementary approach will integrate key components from our six-step validation framework, including empirical evidence from PK and PD data; findings from epidemiological studies; and clinical validation tools, such as drug interaction checkers (Lexicomp, Micromedex) and product monographs (eg, from Health Canada and the US FDA). We will combine these diverse sources of evidence to train the model, aiming to identify patterns that can help prioritize high-risk DDIs for further investigation. We will also use natural language processing (NLP) algorithms to extract important insights from clinical monographs, published research papers, and other medical literature. This step will help us better understand the context around each signal and provide a richer foundation for analysis. Although still exploratory, this method seeks to refine our ability to distinguish clinically significant interactions from spurious associations, ultimately improving how we prioritize potential risks in clinical practice.

We will first use known, previously validated DDIs identified through our six-step validation process to train the model. All sources of evidence collected—including high-throughput computing, PK and PD data, clinical validation tools (eg, drug interaction checkers and product monographs), epidemiological studies, and pharmacovigilance databases—along with insights from the six-step validation framework, will form a comprehensive training dataset for our machine learning model, enabling it to generate risk scores and rank potential interactions based on predicted clinical significance. To ensure robustness, the model will undergo k-fold cross-validation and bootstrap sampling. We will apply interpretability techniques, such as Shapley additive explanations (SHAP), to identify the most influential factors driving each prediction. By automating signal ranking and prioritization, this machine learning approach will explore new opportunities to enhance the identification of clinically meaningful DDIs, supporting safer prescribing and improved postmarket drug surveillance.

